### Participants

We will recruit individuals who meet the study’s eligibility criteria from the waiting list for the physiotherapy and pulmonary rehabilitation service at the University Hospital of the Federal University of Juiz de Fora through telephone or in-person contact. Additionally, individuals from primary healthcare units in the municipality of Juiz de Fora will be invited to participate. Recruitment will be carried out using leaflets distributed at the hospital, university, and on social media. These materials will guide potential participants who consider themselves eligible to contact a researcher involved in the study. Subsequently, a researcher blinded, unaware of the group assignment, will gather initial data to confirm eligibility. All data collection steps will be carried out in the Cardiorrespiratory Laboratory, located at the Faculty of Physiotherapy at Federal University of Juiz de Fora.

### Eligibility criteria

Individuals eligible for inclusion in this study were adults and elderly and had a confirmed diagnosis of COPD based on the criteria outlined by the Global Initiative for Chronic Obstructive Lung Disease (GOLD) [37]. Specifically, patients exhibit a postbronchodilator forced expiratory volume in one second (FEV_1_)/forced vital capacity (FVC) ratio <70% and an FEV_1_ <80% of the predicted value [37]. These individuals must be clinically stable [38] and free from unstable cardiovascular diseases, neurological disorders, or musculoskeletal conditions that might impede the proposed assessments and interventions. The exclusion criteria included individuals unable to perform or comprehend the study assessments due to physical or psychological impairments, those with a primary diagnosis of a respiratory disease other than COPD, individuals requiring oxygen therapy, those with a recent hospitalization within the last 3 months, participants in a physical activity program in the last 6 months, and those with identified cognitive impairment scoring equal to or less than 4 on the Six Item Screener [39].

### Randomization and allocation

Randomization will be performed with a 1:1 allocation ratio for the experimental or control group using random allocation software. The allocation sequence will be kept in identical, opaque, sealed, sequentially numbered envelopes and will remain concealed until the end of the evaluation. The responsible researcher will be instructed not to reveal the group assignments to the physiotherapist or other researchers involved in the study until its completion.

### Blinding

A "double-blind" approach will be adopted, where study participants and researchers responsible for data collection and analysis will be kept blind to the intervention received by each participant. To ensure the integrity of the blinding, an independent committee consisting of trained physiotherapists will be established for each stage of the research. Evaluating and reassessing researchers will not be aware of the intervention assigned to each participant. Instead, another professional will be designated to provide guidance and monitor the intervention, ensuring that the researchers do not have knowledge of the interventions received by the participants.

To ensure participant blinding, both groups will be blinded to the specific intervention. Participants will not be informed about the difference in route guidance, and furthermore, the walkers responsible for guiding the group will be instructed not to discuss or disclose any details of the intervention. This approach creates an environment in which participants have no knowledge or clues revealing the specific nature of the intervention, thus ensuring effective blinding of the study.

For statistical analysis and result interpretation, a researcher will be designated and will be blinded to the intervention assigned to each participant. Patients will not have access to information that could identify treatment groups. This ensures that the researcher cannot influence the results based on expectations or prior knowledge, promoting impartiality in data analysis.

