### Study design

The environment on physical activity for chronic obstructive disease (EPCOT) is a protocol for a parallel, two-group, randomized controlled trial that used concealed allocation with a 1:1 ratio and intention-to-treat analysis designed by independent investigators. The trial was registered at The Brazilian Registry of Clinical Trials (ReBEC) (https://ensaiosclinicos.gov.br, number RBR-4tfwdhp update on 04/12/2024) and follows the guidelines of the *Standard Protocol Items*: *Recommendations for Interventional Trials (SPIRIT)* [35, 36] (S1 Appendix).

The study protocol conformed to the ethical guidelines of the Declaration of Helsinki and was approved by the Research Ethics Committee of University Hospital of the Federal University of Juiz de Fora/MG (Approval Number: #5.889.099, on March 29, 2023). Written informed consent will be obtained from all participants.

Eligible participants received detailed information about the study’s objectives, risks, and benefits from the assessors. After reading and signing the informed consent form (S2 and S3 Appendices), participants provided consent to participate in the study, as established by Resolution 580/2018 of the National Health Council of Brazil. To ensure the privacy and confidentiality of the collected data, appropriate measures will be taken by the entire research team. The principal investigator safeguarded the information’s security by using codes instead of participants’ identifying data and controlling access to electronic files through a unique password. The data collected and analyzed by this Project will be disseminated at congresses and through international peer-reviewed journals and will not be reported in any of the forms of dissemination in this study.

Random sampling will form two groups: an experimental group (ERG), which will engage in physical activity through walking on suggested routes with better walkability, and an active control group (ACG), which will be instructed to choose their own routes. Previously trained researchers will carry out the study. Primary and secondary outcome measures will be assessed two days, 48 hours apart, to prevent participant exhaustion. After an 8-week intervention period, reassessment will be performed (Fig 1).

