### Intervention

Participants allocated to the experimental group will receive personalized and individual routes of better walkability, developed by an architect and urban planner through a virtual urban environmental analysis using the Microscale Audit of Pedestrian Streets (MAPS) [40], to collect audit data on the pedestrian environment and walkability in neighborhoods. The analysis will be performed through a geographical map based on satellite positioning from the participant’s residence. The architect and urban planner will conduct an interview with the participant to detect information that is not identified through virtual urban environmental analysis and will present the suggested routes combined with the participant’s preferences, choices, and acceptance. Participants in this group will receive 5 personalized circuits, with durations of approximately 15 minutes, 20 minutes, 30 minutes, 40 minutes, and 50 minutes, along with distances in kilometers. Each route includes a marked map of the path, a description of the start and end, and information about nearby cultural attractions or commercial areas. On the other hand, the control group will receive only guidance for walking without a specific route suggestion, allowing each participant to freely choose their walking path. The intervention period will last for 8 weeks, and participants will be advised to walk 3 to 5 times a week. The progression will follow the following schedule: in the first week, 15 minutes/day; in the second week, 20 minutes/day; in the third week, 30 minutes/day; in the fourth week, 40 minutes/day; and in the fifth week, 50 minutes/day until the eighth week.

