## Discussion

The evaluation of environmental interventions for individuals with COPD has been limited to a few rigorous studies [32–34]. This study involved a blinded, controlled clinical trial in which participants in the intervention group played an active role in selecting the most suitable walking environment. We outline the rationale and processes of a study that investigates the effectiveness of an environmental intervention involving predefined walking routes in urban areas within the neighborhood, compared to free-form walks, on physical activity and secondary outcomes, including exercise capacity, quality of life, and perceptions of dyspnea, anxiety, and depression. Additionally, we examined the barriers and benefits related to physical activity, exercise motivation, and social engagement in patients with COPD.

While moderate physical activity is highly recommended for individuals with COPD [9], symptoms, physical limitations, social barriers, and motivation often present significant challenges to adherence in this population. A personalized approach that considers environmental, social, and cultural factors to promote physical activity through tailored environmental interventions, accounting for individual differences, preferences, and needs, may enhance adherence and lead to clinical and functional benefits for individuals with COPD.

Several strengths are worth highlighting in this study protocol: i) the intervention is cost-effective and takes place in environments that reduce transportation barriers and costs by being located near the participant’s neighborhood; ii) changes in active behavior will be measured using a validated accelerometer and standardized data extraction; and iii) the protocol incorporates motivational incentive strategies for both groups by offering weekly goals for increasing walking time or the number of steps, monitored by pedometers provided to participants for eight weeks. Participants will also keep their walking and symptom diaries and receive periodic messages or calls for feedback and encouragement to continue walking. In addition, two lectures will be provided on COPD incidence information, symptom management, and the benefits of walking. Although these actions will be offered to both groups, it is possible that combining walking guidance in a favorable environment with participant preferences may result in higher levels of physical activity.

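### The protocol says participants are blind to the intervention they receive, but its own intervention description rules this out; at most they are not told how the groups differ

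*Protocol article*

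**What the plan says.** The Blinding section of the protocol article adopts a double-blind approach in which "study participants and researchers responsible for data collection and analysis will be kept blind to the intervention received by each participant". For participants, the means is non-disclosure: "both groups will be blinded to the specific intervention. Participants will not be informed about the difference in route guidance". Staff are also told not to discuss the intervention. The section concludes that "participants have no knowledge or clues revealing the specific nature of the intervention" and that blinding is therefore effective.

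The Intervention section describes the experimental arm. "The architect and urban planner will conduct an interview with the participant", and "will present the suggested routes combined with the participant’s preferences, choices, and acceptance". "Participants in this group will receive 5 personalized circuits", each with a marked map. Under Study design, the comparator is "an active control group (ACG), which will be instructed to choose their own routes"; the Intervention section confirms that controls get walking advice with no route.

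The Discussion calls the trial blinded and says in the same sentence that "participants in the intervention group played an active role in selecting the most suitable walking environment".

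**The concern.** A person who is interviewed about routes, helps to settle them and is handed maps knows what intervention they have received. The Blinding section therefore states a property that the design, as described elsewhere in the article, does not have.

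This affects how the results can be read. The primary outcome is measured by accelerometer, but it is voluntary behaviour, and expectation can change behaviour. Most secondary outcomes are questionnaires or scales completed by the same participants. A reader who accepts the double-blind label would take performance and reporting bias as controlled by design. The limitations listed in the Discussion do not correct this: they cover changing perceptions of the environment, external events and local conditions, but not participants' awareness of their intervention.

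**Working it through.** No formula applies, and the article gives no figure to reproduce. The check sets the statements side by side.

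**1. Claim against procedure**

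| Blinding section | Elsewhere in the article |
|---|---|
| Participants are blind to the intervention received | Experimental participants are interviewed by the planner, express preferences and accept routes (Intervention) |
| They have no clue to its specific nature | They hold five circuits, each with a marked map (Intervention) |
| The trial is double-blind | Experimental participants actively select their walking environment (Discussion) |

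The right-hand column is the intervention itself. It cannot be concealed from the person receiving it, so the first two claims on the left fail for the experimental arm, and the label fails with them.

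**2. Whether the stated safeguards could still work.** Staff silence cannot hide maps that participants already hold. The safeguard also refers to walkers who guide the group, whereas the Intervention section describes individual walks with indirect supervision by biweekly calls or messages.

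**3. What non-disclosure could achieve.** It could leave participants unaware of what the other group receives, or of which approach is expected to do better. That is masking to the contrast or hypothesis, which is less than the section claims. Even this is uncertain. Study design says eligible participants were given detailed information on the objectives, and the Introduction states the aim as a comparison of a suggested environment with free walking. The consent forms (S2 and S3 Appendices) would show whether the contrast is disclosed, but they are not available here.

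**4. Which outcomes are exposed**
- Primary: accelerometer-measured activity. Reporting bias does not apply; performance bias can.
- Secondary: the instruments under Secondary outcomes are the 6MWT, SGRQ, mMRC, HADS, BREQ-3, LLFDI, EBBS-Brazil and the environmental perception scale, 8 in all. Only the 6MWT is not self-reported, so 8 − 1 = 7 are. The 6MWT still depends on effort.
- Environmental perception is especially exposed, because experimental participants rate their neighbourhood after a planner has shown them routes chosen for walkability.

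The 7 of 8 is a count of exposed instruments. It does not measure bias.

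**The case against.** The best defence is that the section describes a different kind of masking. Participants can know what they do without knowing that another group does something else. This is most plausible for controls, who receive the kit, diary, booklet, education sessions and contacts and see no sign of a route service. The comparator is also active: both groups receive these elements, which narrows differences in attention and expectation. The primary measure is objective, and assessor and analyst blinding is separate and feasible. Unblinded participants are usual in behavioural trials and do not invalidate this one.

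All of this stands, and it limits the point. It does not rescue the text, which claims blindness to the intervention received and the absence of any clue, not merely to the contrast.

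A reader might go further and infer that all participants know their allocation, or that being told the objectives lets them work out their arm. The documents do not support that. They show that experimental participants know the content of what they received. Whether anyone can place that content in one arm of a comparison depends on the consent wording, which is not shown. Nor do the documents show that assessor or analyst blinding fails.

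**Conclusion.** The claim that participants are blind to the intervention received, and with it the double-blind label, is wrong as written: the Intervention section and the Discussion contradict it. This conclusion rests only on the article's own text. What may survive is that participants are not told of the between-group difference, on the assumption that the consent wording does not disclose it.

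The consequence is a misstated risk of bias: possible performance bias for the behavioural primary outcome, and possible reporting bias for seven of eight secondary instruments. Its size and direction cannot be derived from the document, and the active control may reduce it. The sample size, primary measure and analysis model are unaffected. The correction is needed because it changes how the self-reported outcomes can be interpreted.

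**What to change.** - In the Blinding section, replace the double-blind label with: *assessor- and analyst-blinded; participants and intervention staff are aware of the intervention delivered, and participants are not told of the between-group difference in route guidance*. Keep the last clause only if the consent wording supports it.
- Delete the statement that participants have no clues and that blinding is thereby effective.
- Qualify the word blinded in the Discussion in the same way.
- Add participant awareness to the limitations: a possible source of performance bias for the primary outcome, and of reporting bias for the SGRQ, mMRC, HADS, BREQ-3, LLFDI, EBBS-Brazil and environmental perception scale. Interpret those seven accordingly.
- At reassessment, instruct participants not to mention routes to assessors. The Blinding section describes no such instruction, and participants who know their routes could otherwise unmask the assessors.

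The cost is rewording, a less favourable statement of rigour and one brief added instruction.

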### Intervention

Participants allocated to the experimental group will receive personalized and individual routes of better walkability, developed by an architect and urban planner through a virtual urban environmental analysis using the Microscale Audit of Pedestrian Streets (MAPS) [40], to collect audit data on the pedestrian environment and walkability in neighborhoods. The analysis will be performed through a geographical map based on satellite positioning from the participant’s residence. The architect and urban planner will conduct an interview with the participant to detect information that is not identified through virtual urban environmental analysis and will present the suggested routes combined with the participant’s preferences, choices, and acceptance. Participants in this group will receive 5 personalized circuits, with durations of approximately 15 minutes, 20 minutes, 30 minutes, 40 minutes, and 50 minutes, along with distances in kilometers. Each route includes a marked map of the path, a description of the start and end, and information about nearby cultural attractions or commercial areas. On the other hand, the control group will receive only guidance for walking without a specific route suggestion, allowing each participant to freely choose their walking path. The intervention period will last for 8 weeks, and participants will be advised to walk 3 to 5 times a week. The progression will follow the following schedule: in the first week, 15 minutes/day; in the second week, 20 minutes/day; in the third week, 30 minutes/day; in the fourth week, 40 minutes/day; and in the fifth week, 50 minutes/day until the eighth week.

To encourage walking, each participant in both groups received a special kit to assist them in their physical activity and well-being. The kit included a Yamax Pw 610 Pedometer, along with instructions on how to use it correctly. This device measures the number of steps taken during a walking session. Participants will also receive a step diary to record their walking time, the number of steps observed on the pedometer, and their perception of dyspnea and fatigue during the walk using the modified Borg Rating of Perceived Exertion scale [41]. This initiative allows participants to track and monitor their daily progress, motivating them to achieve personal goals and establish healthy habits. Additionally, a booklet containing recommendations such as the benefits of walking, energy conservation techniques, and stretches to be followed will be provided, aiming to optimize the walking experience (S4 Appendix).

Furthermore, two virtual health education sessions will be offered, which will be conducted in the first and third weeks of the intervention through videos or audio; the sessions will be sent to the participants or in a format that best suits their adherence. These educational sessions aimed to deepen participants’ knowledge about COPD, clinical control, symptom management, the importance of correct medication use, and the benefits of walking. This approach aims to empower participants with valuable information, useful tools, and ongoing support so that they can incorporate walking as part of a healthy lifestyle.

Throughout the program, both groups will receive indirect supervision through biweekly phone calls or text messages, where a professional will be available to answer questions, motivate, and monitor the progress of each individual.

### Sample characterization

To obtain a more precise characterization of the patient’s socioeconomic situation, the questionnaire of the Economic Classification Criteria of Brazil [42] was used. This instrument consists of a series of questions and is widely used in studies involving the Brazilian population. The questionnaire assesses the socioeconomic level of families, considering items such as purchasing power, possession of durable goods, and the level of education of the head of the family. Additionally, the Six Item Screener Scale [39] will be used to screen for cognitive impairment, involving words and questions related to temporal orientation.

Lung function will be measured by spirometry to confirm obstructive ventilation disorder in patients with COPD using a portable spirometer (Spirobank II, Medical International Research, New Berlin, USA) to obtain variables such as forced vital capacity (FVC), forced expiratory volume in the first second (FEV_1_), and the FEV_1_/FVC ratio, expressed in both absolute values and as a percentage of the predicted value [43]. Participants will be instructed to perform three maximum forced expiratory maneuvers, maintaining expiration during the expiratory flow period. We will strictly adhere to the acceptance and reproducibility criteria proposed by the guidelines [44] to ensure the quality of the examinations.

The Charlson comorbidity index [45], a tool that covers 19 different clinical conditions, was used to assess the presence of comorbidities. Each condition was categorized and scored based on its prognostic impact and associated mortality. For each group of clinical conditions, a relative risk was assigned, and these risks were converted into scores ranging from 0 to 6. Additionally, each patient’s age range is associated with a score ranging from 1 to 4. Thus, the result is obtained by summing the scores assigned to each clinical condition and the patient’s age range. A higher final score indicates a greater impact of comorbidities and a greater risk of complications on the patient’s prognosis.

The impact of COPD symptoms will be assessed using the COPD Assessment Test (CAT) [46], an instrument that quantifies how COPD symptoms affect the daily lives of patients. The CAT comprises eight items addressing various aspects of symptoms, including cough, sputum production, chest tightness, shortness of breath, limitations in daily activities, confidence in leaving the house, sleep quality, and energy level. CAT results can vary and are classified in terms of the clinical impact of symptoms as follows: 6–10 points (mild), 11–20 points (moderate), 21–30 points (severe), and 31–40 points (very severe) [46].

